**Introduction/Context:**

It is estimated that chronic venous disease in the lower extremities (e.g. varicose veins) is one of the most common pathological conditions in adults within industrialized countries, affecting ~40% of the population. Chronic venous disease can encompass numerous pathologies whose casual factors can be both genetic and/or environmental and express a wide scope of symptomatic presentations from ulcers, deep vein thrombosis, and varicose veins. The latter refers to a tortuous or twisted vein(s) that may be visibly enlarged or protrude physically due to the engorgement of blood within the peripheral lower limb vasculature. Mechanically, this deformation and poor blood flow is related to the reduction in tensile strength and function of veins leaflets that typically ensure a unidirectional movement of blood. The loss of leaflet function causes blood reflux, localized pooling, and architectural obstructions which give rise to varicose veins.

Within Canada treatments for varicose veins can be segmented into two regulatory sections, the Therapeutic Products Directorate (TPD) that oversees drug and medical device usage and the Natural and Non-prescription Health Products Directorate (NNHPD) that oversees products deemed to originate from natural sources rather than human-derived innovations. With respect to NNHPD products and varicose veins, plant extracts from witch-hazel (*Hamamelis virginiana*) and horse-chestnut (*Aesculus hippocastanum*) are the primary natural medicinals used to treat this condition. The sponsor (Delivra Inc.) currently holds a Natural Product Number (NPN) license for the manufacturing and sales of topical LivRelief™-Varicose (NPN 80029345) that includes 10% (w/w) witch-hazel. In keeping with the vast majority of NPNs the efficacy of this hinges upon the ingredients-specific Health Canada monograph for topical witch-hazel. This is the inverse to TPD drugs, which undergo rigorous product-specific testing to generate a product-specific monograph.

Recently, the NNHPD has signaled a broad reconstruction of its claim system to better distinguish those products that have undergone product-specific clinical testing as opposed to those which rely upon ingredient-specific monographs. The underlying goal is to provide the Canadian consumer with sufficient scientifically-underpinned information and labeling to make informed purchases. With this in mind, the sponsor (Delivra Inc.) is interested in completing an study of its current product for its current claim within the scope and limitations as described by the product license. In essence, a Phase-IV interventional pilot study is proposed.

**Safety and Adverse Events**

As licensed, if varicose veins persist or worsen after or during the course of treatment consult a healthcare practitioner, such as the Primary Investigator. In rare cases the license product may cause a skin rash. This rash is a known adverse event of the licensed product and use of the product should be discontinued immediately. More recently and not encompassed by the products licensing of federal monograph, several natural extracts (including witch-hazel) have been shown to cause contact dermatitis in some individuals. As such, any acute or progressive skin inflammation is sufficient to warrant discontinuation of product use.

#### **Absorption and Plasma Level:**

To our knowledge there is no scientific information (peer-reviewed or otherwise) regarding the topical absorption, distribution, metabolism, or excretion of witch-hazel extract or a component thereof.

#### **Study purpose and rational:**

LivRelief Varicose Vein Cream is a Natural Health Product product licensed as a treatment for venous stasis (NPN 80029345). This phase IV interventional pilot study aims to collect information on specific objective and subjective measures by the sponsor. Quality of Life is measured through the Quality of Life Enjoyment and Satisfaction Questionnaire – Short Form (Q-LES-Q-SF). In combination and complementary to this questionnaire, the Venous Clinical Severity Score (VCSS) is employed whose construction was targeted directly at repeat longitudinal evaluations. A preliminary dataset (N=30) is proposed in order to evaluate product use and data collection quality.

#### **Description of the population to be studied (inclusion/exclusion criteria)**

Once a signed consent is obtained, the participant is enrolled in the study and screened for the presence of varicose veins as defined by the chronic venous disorders Clinical-Etiology-Anatomy-Pathophysiology (CEAP) classification system as (1) demonstrating a Varicose Veins score >0 at the prospective site of product application and (2) demonstrating an Active Ulcer Number equal to zero at the prospective site of product application.

##### *Inclusion Criteria:*

- Participants at least 19 years of age or older.
- Participants with lower limb varicose veins.

##### *Exclusion Criteria*

- Allergy to witch-hazel or any allergies in the cream.
- Intent to undergo surgical treatment varicose veins within the next six weeks.
- Pregnant or breastfeeding or planning to be pregnant.

- Any Dementia or Major Cognitive dysfunction that would preclude the individual's ability to provide informed consent or complete the Case Report Form.
- Any unstable medical condition (including but not limited to cardiovascular, cardiac/hypertension disease, moderate to severe kidney disease, and moderate to severe liver disease)
- Any medical condition that would preclude the participant's or a caregiver's ability to administer the product on a daily basis for the time period required to complete the study.
- An active ulcer at the site of product application (as evaluated during CEAP screening).

#### **Participant Recruitment and Advertising:**

Patients of the Mayer Institute suffering of varicose veins will be offered to participate in the study. Participants will also be recruited through advertisements (posters) at The Mayer Institute in Hamilton. The participant will contact the study investigator (they physician) and make an appointment to discuss the study and obtain consent. Each participant will be initially screened by a trained research coordinator, and then assessed by the principal investigator for health history and meeting of the inclusion criteria and ensure they do not meet any of the exclusion criteria (see below).

#### **Study Design and Methodology:**

The present study is designed as a phase IV interventional pilot study.

#### **Statistical Analysis:**

As described by Thabane et al. (2010), we have assigned success criteria based on the following feasibility objectives:

- At least 70% of all eligible participants can be recruited
- Complete full data collection in at least 70% of all recruited participants

#### **Dose and Mode of Administration:**

Each day of the Experimental test period (6 weeks or 42 days) 1.0 mL (one pumps) of the product is applied to the varicose vein and surrounding area twice a day. This dosage is in alignment with the products licensed use.

#### **Product and Ingredients' List:**

The "LivRelief- Varicose Vein Cream" is being used for this study:

- NPN#: 80029345.
- List of ingredients:
  - **Active Ingredient:** Hamamelis virginiana L. (Witch Hazel) bark 10%

- **Non-Medicinal Ingredients:** Aesculus Hippocastanum (Horse Chestnut) Seed Extract, Arnica Montana Flower Extract, Black currant seed oil, Butylene Glycol, Carnauba Wax, Cetearyl olivate, Cetyl Palmitate, Chlorphenesin, Citrus limon extract, Dicaprylyl carbonate, Ethoxydiglycol, Glycerin, Goldenrod extract, Lecithin, Peucedanum ostruthium Leaf extract, Polyacrylate-13, Polyisobutene, Polysorbate 20, Purified water, Rosemary extract, Rubus idaeus (Raspberry) Seed oil, Ruscus Aculeatus Root Extract, Rutin, Sambucus nigra flower extract, Sorbitan Palmitate, Sorbitan olivate, Sunflower oil, Xanthan Gum, sodium phytate

### **Definition of endpoints:**

#### *Primary:*

- Collection of data and completeness of datasets.

#### *Exploratory analysis:*

- Evaluation of statistical differences (if any) in objective and/or subjective measures at onset and completion of the trial.

### **Measurements and measurement instruments:**

A combination of Objective and Subjective methods will be employed in this interventional study.

#### *Objective measures:*

- Circumferential measurements of the limb will be collected at onset and completion (twice) of the trial.  
Three landmarks will be used on the leg:
  - Mid foot
  - 5 cm proximal to the medial malleolus
  - 5 cm distal from the tibial tuberosity
- Photographic evidence of the discoloration of the skin in the vicinity of the varicose vein/limb along with incremental (metric) measure in frame. Photographic information will be collected at onset and completion (twice) of the trial.

#### *Subjective measures:*

- Clinical grade, Etiology, Anatomy, and Pathophysiology (CEAP) classification of the varicosity. The CEAP classification is assessed at onset and completion (twice) of the trial.
- Quality of Life Enjoyment and Satisfaction Questionnaire – Short Form (Q-LES-Q-SF) is recorded as Quality of Life questionnaire. The Q-LES-Q-SF is administered at onset and completion (twice) of the trial.

- Venous Clinical Severity Score (VCSS). The VCSS is assessed at onset and completion (twice) of the trial.
- Adverse events collection as self-reported incidents at the completion of trial and specific inquiries in regards to any adverse events at the site of administration, including rashes.

### Schedule of Assessments

As described in Table 2, on Day 1 of the study the participant completes the Informed Consent Form (ICF), is evaluated according to inclusion and exclusion criteria, undergoes CEAP classification of the region in question, photographed within and limited to the region in question, limb diameter measurement, and Q-LES-Q-SF in this chronological order. On the same day and subsequent to these evaluations and measures the product is applied for the first time (Day 1) and materials and instructions are provided for self-administration over the proceeding period (41 days).

At the end of six weeks (42 days +/- 3 days) the same schedule of assessments is administered (with the exception of consent and inclusion/exclusion) as well as self-reported adverse events, if any.

**Table 2 Graphical Schedule of Assessments**

| EVENT (maximum duration)                                                              | Screening and Baseline
Visit 1
(Day 1) | Experimental
Period
(Day 2-40) | End Visit
Visit 2
(Day 42) |
|----------------------------------------------------------------------------------------------|-------------------------------------------------------|-----------------------------------------------|-------------------------------------------|
| Informed Consent Form (2 minutes)                                                            | ✓                                                     |                                               |                                           |
| Pregnancy Test (5 minutes)                                                                   | ✓                                                     |                                               |                                           |
| Inclusion/Exclusion Criteria Evaluation (2 minutes)                                          | ✓                                                     |                                               |                                           |
| Leg Circumferential measurement (5 minutes)                                                  | ✓                                                     |                                               | ✓                                         |
| Skin Discoloration assessment (photography) (2 minutes)                                      | ✓                                                     |                                               | ✓                                         |
| CEAP Classification (5 minutes)                                                              | ✓                                                     |                                               | ✓                                         |
| Quality of Life Enjoyment and Satisfaction
Questionnaire – Short (Q-LES-Q-SF) (2 minutes) | ✓                                                     |                                               | ✓                                         |
| Venous Clinical Severity Score (VCSS) (3 minutes)                                            | ✓                                                     |                                               | ✓                                         |
| Cream Application (twice a day) (<1 minute)                                                  | ✓                                                     | ✓                                             |                                           |

A Phase IV Interventional Pilot study of a licensed topical product for the treatment of varicose  
veins in adults  
Protocol V3 – April 2017

|                           |   |   |   |
|---------------------------|---|---|---|
| Adverse Events Evaluation | ✓ | ✓ | ✓ |
|---------------------------|---|---|---|

**Introduction/Context:**

It is estimated that chronic venous disease in the lower extremities (e.g. varicose veins) is one of the most common pathological conditions in adults within industrialized countries, affecting ~40% of the population. Chronic venous disease can encompass numerous pathologies whose casual factors can be both genetic and/or environmental and express a wide scope of symptomatic presentations from ulcers, deep vein thrombosis, and varicose veins. The latter refers to a tortuous or twisted vein(s) that may be visibly enlarged or protrude physically due to the engorgement of blood within the peripheral lower limb vasculature. Mechanically, this deformation and poor blood flow is related to the reduction in tensile strength and function of veins leaflets that typically ensure a unidirectional movement of blood. The loss of leaflet function causes blood reflux, localized pooling, and architectural obstructions which give rise to varicose veins.

Within Canada treatments for varicose veins can be segmented into two regulatory sections, the Therapeutic Products Directorate (TPD) that oversees drug and medical device usage and the Natural and Non-prescription Health Products Directorate (NNHPD) that oversees products deemed to originate from natural sources rather than human-derived innovations. With respect to NNHPD products and varicose veins, plant extracts from witch-hazel (*Hamamelis virginiana*) and horse-chestnut (*Aesculus hippocastanum*) are the primary natural medicinals used to treat this condition. The sponsor (Delivra Inc.) currently holds a Natural Product Number (NPN) license for the manufacturing and sales of topical LivRelief™-Varicose (NPN 80029345) that includes 10% (w/w) witch-hazel. In keeping with the vast majority of NPNs the efficacy of this hinges upon the ingredients-specific Health Canada monograph for topical witch-hazel. This is the inverse to TPD drugs, which undergo rigorous product-specific testing to generate a product-specific monograph.

Recently, the NNHPD has signaled a broad reconstruction of its claim system to better distinguish those products that have undergone product-specific clinical testing as opposed to those which rely upon ingredient-specific monographs. The underlying goal is to provide the Canadian consumer with sufficient scientifically-underpinned information and labeling to make informed purchases. With this in mind, the sponsor (Delivra Inc.) is interested in completing an study of its current product for its current claim within the scope and limitations as described by the product license. In essence, a Phase-IV interventional pilot study is proposed.

**Safety and Adverse Events**

As licensed, if varicose veins persist or worsen after or during the course of treatment consult a healthcare practitioner, such as the Primary Investigator. In rare cases the license product may cause a skin rash. This rash is a known adverse event of the licensed product and use of the product should be discontinued immediately. More recently and not encompassed by the products licensing of federal monograph, several natural extracts (including witch-hazel) have been shown to cause contact dermatitis in some individuals. As such, any acute or progressive skin inflammation is sufficient to warrant discontinuation of product use.

**Absorption and Plasma Level:**

To our knowledge there is no scientific information (peer-reviewed or otherwise) regarding the topical absorption, distribution, metabolism, or excretion of witch-hazel extract or a component thereof.

**Study purpose and rational:**

LivRelief Varicose Vein Cream is a Natural Health Product licensed as a treatment for venous stasis (NPN 80029345). This phase IV interventional pilot study aims to collect information on specific objective and subjective measures by the sponsor. Quality of Life is measured through the Quality of Life Enjoyment and Satisfaction Questionnaire – Short Form (Q-LES-Q-SF). In combination and complementary to this questionnaire, the Venous Clinical Severity Score (VCSS) is employed whose construction was targeted directly at repeat longitudinal evaluations. A preliminary dataset (N=30) is proposed in order to evaluate product use and data collection quality.

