#### **Statistical Analysis:**

As described by Thabane et al. (2010), we have assigned success criteria based on the following feasibility objectives:

- At least 70% of all eligible participants can be recruited
- Complete full data collection in at least 70% of all recruited participants

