### **Definition of endpoints:**

#### *Primary:*

- Collection of data and completeness of datasets.

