#### *Exploratory analysis:*

- Evaluation of statistical differences (if any) in objective and/or subjective measures at onset and completion of the trial.

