#### *Objective measures:*

- Circumferential measurements of the limb will be collected at onset and completion (twice) of the trial.  
Three landmarks will be used on the leg:
  - Mid foot
  - 5 cm proximal to the medial malleolus
  - 5 cm distal from the tibial tuberosity
- Photographic evidence of the discoloration of the skin in the vicinity of the varicose vein/limb along with incremental (metric) measure in frame. Photographic information will be collected at onset and completion (twice) of the trial.

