#### *Subjective measures:*

- Clinical grade, Etiology, Anatomy, and Pathophysiology (CEAP) classification of the varicosity. The CEAP classification is assessed at onset and completion (twice) of the trial.
- Quality of Life Enjoyment and Satisfaction Questionnaire – Short Form (Q-LES-Q-SF) is recorded as Quality of Life questionnaire. The Q-LES-Q-SF is administered at onset and completion (twice) of the trial.

A Phase IV Interventional Pilot study of a licensed topical product for the treatment of varicose  
veins in adults  
Protocol V4 – May 2017

- Venous Clinical Severity Score (VCSS). The VCSS is assessed at onset and completion (twice) of the trial.
- Adverse events collection as self-reported incidents at the completion of trial and specific inquiries in regards to any adverse events at the site of administration, including rashes.

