### Schedule of Assessments

As described in Table 2, on Day 1 of the study the participant completes the Informed Consent Form (ICF), is evaluated according to inclusion and exclusion criteria, undergoes CEAP classification of the region in question, photographed within and limited to the region in question, limb diameter measurement, and Q-LES-Q-SF in this chronological order. On the same day and subsequent to these evaluations and measures the product is applied for the first time (Day 1) and materials and instructions are provided for self-administration over the proceeding period (41 days).

At the end of six weeks (42 days +/- 3 days) the same schedule of assessments is administered (with the exception of consent, pregnancy test and inclusion/exclusion) as well as self-reported adverse events, if any.

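### Evaluating product use is a stated reason for the N=30 dataset, but Protocol V4 specifies no measure, endpoint or success criterion for use during 41 days of self-administration

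*Supplement*

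**What the plan says.** All references are to Protocol V4 (May 2017), the latest version in the Supplement.

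- **Purpose.** The section on study purpose and rationale says: "A preliminary dataset (N=30) is proposed in order to evaluate product use and data collection quality". The same section also gives a wider aim of collecting objective and subjective measures.
- **Who applies the product.** Under Schedule of Assessments, the first application is on Day 1, after the baseline assessments; then "materials and instructions are provided for self-administration over the proceeding period (41 days". Table 2 has two visits, Day 1 and Day 42, and none between them.
- **Primary endpoint.** "Collection of data and completeness of datasets".
- **Success criteria (Statistical Analysis).** "At least 70% of all eligible participants can be recruited" and "Complete full data collection in at least 70% of all recruited participants".
- **Exploratory analysis.** "Evaluation of statistical differences (if any) in objective and/or subjective measures at onset and completion of the trial".
- **Measures.** The objective list holds limb circumference ("Circumferential measurements of the limb will be collected at onset and completion (twice) of the trial") and photographs. The subjective list holds CEAP, Q-LES-Q-SF, VCSS and adverse events ("Adverse events collection as self-reported incidents at the completion of trial", with specific inquiry about the application site, including rashes).
- **Dose section.** One pump of 0.8 mL, twice a day, for 42 days.

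**The concern.** The purpose sentence names two things to be evaluated. Data collection quality is carried through to the primary endpoint and to a 70% criterion. Product use is carried through to nothing.

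This matters because use is unobserved for almost the whole study and early stopping is foreseen: the safety section calls for discontinuation on rash or skin inflammation. A person who stops can still attend Visit 2, undergo every assessment and count as fully collected data. The pilot could then be declared feasible without anyone knowing whether participants will apply the cream twice a day for six weeks, which a later trial would need to know. If the exploratory comparison shows no change, the sponsor could not say whether the cream was used without visible change or was not used.

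**Working it through.** No sample-size calculation can be reproduced: N=30 is given without alpha, power, effect size or precision target, and the point does not depend on one. The check is a search for a use variable, followed by simple arithmetic on planned use.

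**Step 1. Is use recorded anywhere in V4?**

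| Place in V4 | Content | Records use? |
|---|---|---|
| Objective measures | Circumference, photographs | No |
| Subjective measures | CEAP, Q-LES-Q-SF, VCSS, adverse events | No |
| Table 2, other rows | Consent, pregnancy test, eligibility, and the measures above | No |
| Table 2, cream application row | Ticked for Day 1 and Day 2-40, not for Visit 2 | No; it shows when cream is to be applied |
| End visit text | Baseline assessments repeated, plus self-reported adverse events | No |
| Primary endpoint | Data collection and completeness | No |
| Success criteria | Recruitment, full data collection | No |
| Exploratory analysis | Onset against completion | No |

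Measures of actual use specified: 0. There is no diary, container count or weight, product return, use question or definition of adherence.

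**Step 2. Planned use per participant** = days × 2 applications × 0.8 mL.

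- Dosing text, 42 days (Day 1 plus 41): 42 × 2 = 84 applications; 84 × 0.8 = 67.2 mL.
- Table 2 ticks, Day 1 plus Days 2-40, 40 days: 40 × 2 = 80 applications; 80 × 0.8 = 64.0 mL.
- If use runs to the end visit, whose window is 42 ± 3 days: 39 × 2 × 0.8 = 62.4 mL to 45 × 2 × 0.8 = 72.0 mL.

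The text and Table 2 disagree: Day 41 falls in no column and Day 42 is not ticked for cream.

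**Step 3. What the plan could fail to see.** A participant who made only the first application used 0.8 mL, which is 0.8 / 67.2 = 1.2% of the text total, or 0.8 / 64.0 = 1.25% of the Table 2 total. If that person has no adverse event and attends Visit 2, no specified field differs because of the non-use. With 30 recruited, the completeness criterion needs 0.70 × 30 = 21 complete datasets. Neither that count nor the recruitment percentage depends on how much cream those people used.

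**Step 4. What an added endpoint could show.** Exact (Clopper-Pearson) 95% intervals for a proportion with n = 30:

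- 21/30 = 70%: 50.6% to 85.3%
- 27/30 = 90%: 73.5% to 97.9%

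These counts are illustrative. Such an endpoint could separate generally good use from generally poor use, but not fine gradations.

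**The case against.** **Product use may mean experience with the product, not adherence.** The phrase is undefined, and the site-specific adverse-event inquiry and before-after measures address the broader reading in part. That stands as a limit. But those data do not show whether or how much cream was applied, and even tolerability is hard to read without exposure.

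**The Case Report Form may ask about use.** V4 mentions a form that participants must be able to complete, and its content is not shown. So the supportable statement is that the protocol specifies no use measure, not that none exists. Even if one does, no endpoint or criterion draws on it.

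**The primary endpoint does not need use data.** True. Recruitment and completeness can be assessed without it.

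Four stronger readings are tempting and should not be adopted:

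- *Half of the study's purpose cannot be answered.* This fits only the one sentence; the aim of collecting objective and subjective measures is served.
- *Every early stopper looks identical to a full user.* Someone who stops for a rash should show up in the adverse-event data. Only stopping without an event is invisible.
- *No before-after result could be interpreted.* A change under ordinary self-use can still be described as such. The clearer loss is for a null result; for a positive one, the larger obstacle is that V4 describes no comparison group, and use data would not mend that.
- *Planned use is 67.2 mL.* It is one of two totals that V4 supports.

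**Conclusion.** The point holds as a gap between a stated aim and what the protocol specifies. Following V4 exactly leaves the evaluation of product use without data on use. Both 70% criteria could be met with little product applied, and a null exploratory finding could not be separated from non-use.

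The gap is complete for adherence and exposure: no measure is specified against a planned 64.0 or 67.2 mL per participant. It does not undermine the primary completeness endpoint, so it should be corrected but does not invalidate the design.

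The conclusion assumes that product use includes at least whether and how much cream was applied, and that the Case Report Form adds nothing beyond the protocol text. If the form does hold a use question, the remaining defect is that no endpoint or criterion uses it.

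**What to change.** 1. **Reconcile the planned days** between the dosing and schedule text (42 days) and Table 2 (Day 1 plus Days 2-40), so that planned use has one denominator. Which is right is for the sponsor and investigator to settle.
2. **Define product use** in the purpose section.
3. **Add a Visit 2 question**: date of last application and number of days missed.
4. **Weigh the pump once at dispensing (Day 1) and once at return (Visit 2).** Report the difference as product dispensed: it does not prove application to the leg, and conversion from grams to mL needs a product density that V4 does not give.
5. **Add a descriptive feasibility endpoint**: the proportion of participants reaching a pre-stated share of planned use, with an exact 95% confidence interval. State how an unreturned pump is counted and how the end-visit window is handled.
6. **Do not analyse before-after change by amount used as evidence of effect.** With at most 30 people, people who stop because of a rash or lack of benefit would fall in the low-use group. If shown at all, label it descriptive and confounded.

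Cost: a simple scale, a few Case Report Form fields and a few more minutes at each of the two existing visits. Participants must bring the pump back, and some will not, so the use endpoint may itself have missing values; the Visit 2 question is the fallback. No visit is added and no clinical rule changes.
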